## Abstract

**Introduction:**

Chronic spontaneous urticaria (CSU) is a common skin condition that can significantly impact patients’ quality of life. Although studies have demonstrated the efficacy of acupuncture in treating CSU, the underlying mechanisms remain unclear. Dysfunction within the brain’s default mode network (DMN) represents a fundamental characteristic of central pathological changes associated with CSU. Therefore, it is hypothesized that improving brain network dysfunction could serve as a key mechanism through which acupuncture exerts its therapeutic effects. This study aims to provide evidence supporting this hypothesis.

**Methods and analysis:**

This study, a parallel, randomized, sham-controlled functional neuroimaging investigation will be conducted in China. We aim to enroll 50 patients with CSU and 25 healthy controls, distributing them evenly between the acupuncture and sham acupuncture groups in a 1:1 ratio. The total observation period will span 6 weeks, including 2 weeks designated for the baseline phase and 4 weeks allocated for the clinical treatment phase. Prior to treatment, all participants will undergo magnetic resonance scanning, clinical index detection, and microbiota collection. Following treatment, the patients with CSU will be retested for these indicators. Using resting-state functional connectivity (rsFC) analysis, dynamic Functional Connection (dFC) analysis, and brain microstate extraction technology combined with correlation analysis of microbiota and clinical indicators, the regulatory mechanism of acupuncture on the brain network of CSU will be evaluated from multiple dimensions.

**Ethics and dissemination:**

This trial was approved by the Biomedical Ethics Review Committee of the West China Hospital, Sichuan University (No. 2022-1255). Each participant will provide written informed consent to publish any potentially identifiable images or data.

**Clinical trial registration**https://www.chictr.org.cn/, identifier: ChiCTR2200064563.

## Introduction

Chronic urticaria (CU) is a skin disease characterized by reddish wheals and unbearable itching, with or without angioedema, lasting for ≥6 weeks. Chronic spontaneous urticaria (CSU) is the most common type of CU (71.2%) and is characterized by urticaria symptoms without inducing factors (1, 2). The prevalence of CU is particularly high within the Asian population (1.5%), with a higher prevalence among women than men (3). Owing to complicated conditions, recurrent symptoms, and few effective curative treatments, patients are often required to take high-cost drugs for an extended period. This significantly impacts their quality of life and places a considerable burden on both individuals and society (4, 5).

The latest clinical guidelines for urticaria state that modern second-generation H1-antihistamines should be employed as first-line treatment drugs (2). Despite this, the guidelines do not provide specific recommendations for individual specific drugs due to insufficient research on the effectiveness and safety evaluation of all second-generation H1-antihistamines. Furthermore, the guidelines recommend using omalizumab or cyclosporine for patients who have an inadequate response to second-generation H1-antihistamines. However, there are still some patients who do not benefit from these medications (6, 7). The Taiwanese Dermatological Association consensus proposes that non-pharmacological therapies are also an important approach in alleviating urticaria (8). As an nondrug alternative therapy, acupuncture has been widely used to treat pruritic dermatoses, including CSU, and has demonstrated curative effects (9, 10). However, due to a lack of high-quality evidence supporting its use and insufficient elucidation on the mechanisms underlying acupuncture’s effects, recent clinical practice guidelines do not recommend or report the beneficial effect of acupuncture on CSU (11, 12). Therefore, further research is needed to provide additional evidence.

Given the multi-target and holistic regulatory characteristics of acupuncture, single-mechanism studies cannot fully elucidate the mechanism underlying its therapeutic effects. Therefore, the objective of this study is to explore the potential therapeutic targets of acupuncture by examining a systematic onset mechanism on CSU. Functional magnetic resonance imaging (fMRI) studies have demonstrated that during episodes of dermatotic itch in patients, the primary afferent nerves from the skin projects itch signals to the thalamus. These signals activate the brain’s default mode network (DMN) (13, 14), leading to abnormal functional connectivity. It has been established that DMN brain dysfunction represents an important characteristic of central pathological changes in CSU (15, 16). Moreover, Characteristic changes have been reported in the intestinal microbial population of patients with CSU (17), which may aggravate inflammatory responses and immune dysfunction (18). Similar to gut microbiota, the skin microbiota is closely associated with chronic inflammatory skin diseases (19–21). It plays a regulatory role in modulating immune responses within the skin to prevent inflammation (22). Furthermore, a bidirectional interaction between the microbiota and brain function, often referred to as the “Microbiota-Brain Axis,” has been identified (23). This interaction may potentially contribute to the pathogenesis of certain chronic inflammatory skin conditions like rosacea (24), and can influence neurophysiology and behavior, including anxiety and depression. These effects involve complex mechanisms involving the immune system, neuroendocrine system, and metabolism (25). However, a comprehensive understanding of these mechanisms remain elusive. Another objective of this study is to enhance the understanding of the underlying pathological mechanisms involved in CSU from diverse perspectives.

Recent studies on brain networks have shown that DMN largely overlaps with acupuncture response areas (26, 27). That is, verum acupuncture can regulate the DMN and increase the functional connectivity of the DMN with the sensorimotor network, pain emotion, and memory-related brain regions. Moreover, acupuncture can exert therapeutic effects by modulating microbiota (28, 29). These underlying mechanisms also play a crucial role in both the development and resolution of CSU. Accordingly, we have designed a randomized sham acupuncture-controlled trial. fMRI will serve as the primary research method while the key DMN brain regions regulated by acupuncture for CSU treatment will represent the seed points. Furthermore, we plan to analyze the microbiota and clinical indicators. The primary objective of this study is thus to systematically elucidate the brain network mechanism associated with the treatment of CSU by acupuncture. Our goal is to provide robust scientific evidence to support the clinical application of acupuncture as a treatment modality for CSU.

## Methods and analysis

### Study design

This is a parallel randomized sham-controlled functional neuroimaging study. Fifty CSU patients and 25 matched healthy subjects will be randomly assigned to the verum or sham acupuncture groups at a 1:1 ratio. The total observation period of this study is 6 weeks, including a baseline period of 2 weeks and a clinical treatment period of 4 weeks. Before treatment, all participants (*n* = 75) will undergo clinical index evaluation, magnetic resonance scanning, and microflora collection. Following treatment, only the CSU patients will be reassessed for these indicators. The study flow chart is presented in Figure 1, and the schedule of enrolment, interventions, and assessments is shown in Table 1. This trial will be reported following the Standard Protocol Items: Recommendations for Interventional Trials (SPIRIT).

**Figure 1 fig1:**
[figure not shown]
Flow diagram.

**Table 1 tab1:** Schedule of enrolment, interventions, and assessments.

Time point	Enrolment	Baseline	Treatment period	
	Week-1	Week 0	Week 2	Week 4
**Enrolment**				
Eligibility screen	√			
Informed consent	√			
Inclusion/exclusion criteria	√			
Expectation of acupuncture	√			
Physical examination	√	√	√	√
Medication record	√	√	√	√
Treatment record	√	√	√	√
**Intervention groups**				
Verum acupuncture				
Sham acupuncture				
**Assessments**				
UAS7/VAS		√	√	√
PSQI/DLQI		√	√	√
HAMA/HAMD		√	√	√
SAS/SDS		√	√	√
Skin wheal measures		√	√	√
IgE/CRP		√		√
fMRI		√		√
Gut/skin microbiota		√		√
**Safety**				
Safety evaluation			√	√
Adverse events				√
Effects self-assessment				√
Patient compliance				√
Blinding assessment				√

### Recruitment and informed consent

Participants will be recruited from the West China Hospital of Sichuan University from 1 January 2022 to 31 December 2023. Different strategies will be used to recruit potential participants, including posters and social media advertisements. Researchers will ensure that the participants are fully informed regarding the research procedures, benefits, and potential risks. Those who agree to participate will provide written informed consent before beginning the study and will be made aware that they can withdraw at any time.

### Participants

#### CSU patients

##### Diagnosis criteria

According to the diagnostic criteria of CSU in “the International EAACI/GA^2^LEN/EuroGuiDerm/APAAACI guidelines for the definition, classification, diagnosis, and management of urticaria” (2021 edition) (2): (1) repeat appearance of wheals, (2) with/without angioedema, (3) wheal episodes ≥2 times per week, (4) recurrent attacks ≥6 weeks, and (5) spontaneous wheals induced by nonspecific stimulation factors.

##### Inclusion criteria

The study will enroll patients who meet the following criteria (1) meet the diagnostic criteria of CSU as defined in “The international EAACI/GA^2^LEN/EuroGuiDerm/APAAACI guideline for the definition, classification, diagnosis, and management of urticaria” (2); (2) right-handedness of either sex, aged between 18 and 70 years, with a minimum of 6 years of education; (3) urticaria activity score 7 (UAS7) > 14; (4) no metal implants, no fMRI scanning contraindications; (5) patients who have not taken any antihistamines within 2 weeks before entering the study, and have not used steroid hormones or immunosuppressants within the last month; (6) no acupuncture treatment within 3 months before entering the study, no participation in other ongoing clinical studies; (7) and patient who have provided signed informed consent and volunteered to participate in this study.

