##### Exclusion criteria

Patients who meet any of the following criteria will be excluded: (1) claustrophobic or other fMRI scanning contraindications; (2) unable to understand or record in the urticaria diary; (3) pregnant or lactating; (4) severe primary diseases, such as cardiovascular, liver, kidney, digestive, or hematopoietic conditions; (5) progressive malignant tumors or other severe wasting diseases that increase the risk of concurrent infection and bleeding; (6) unconscious, unable to express subjective symptoms independently, or diagnosed with a psychiatric illness; (7) and patients who have participated in similar research within the past month.

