#### Healthy controls

##### Inclusion criteria

Participants who meet all of the following criteria will be included in this study: (1) have not participated in similar research within 1 month; (2) right-handedness of either sex; between the ages of 18 and 70 years, with a minimum of 6 years of education; (3) no history of urticaria or other allergic diseases; (4) no drug use for at least 15 days before entering the study; (5) no metal implants, no fMRI scanning contraindications; (6) all physiological indexes are common, no functional or organic diseases; (7) No participation in similar or other clinical studies; (8) volunteer for this study and provide signed informed consent.

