#### Microbiota analysis

Clinical skin and intestinal flora DNA will be analyzed using 16S rDNA amplicon sequencing to determine the microbial composition of the samples. 16S rRNA gene sequencing will be performed using Novogene (Beijing, China), according to the manufacturer’s instructions. Raw data obtained by sequencing will then be spliced and filtered to obtain clean data. The DADA2 method will be employed to reduce noise based on the effective data, and sequences with abundances <5 will be filtered out to obtain the final amplicon sequence variants (ASVs).

For the ASVs obtained, species annotation will be performed on representative sequences to obtain the corresponding species information and abundance distribution. Simultaneously, the abundance, alpha diversity calculation, Venn diagrams, and petaline graphs of ASVs will be analyzed to obtain species richness and evenness information. Additionally, multiple sequence alignment of ASVs will be carried out to construct a phylogenetic tree. Principal coordinate analysis (PCoA), principal component analysis (PCA), nonmetric multi-dimensional scaling (NMDS), other dimension reduction analysis, and sample phylogenetic tree display will be applied to explore the differences in community structure between CSU patients and healthy people, and between the acupuncture group and sham acupuncture group. To further explore the community structure differences among grouped samples, statistical analysis methods, including *t*-test, MetaStat, and LEfSe, will be employed to test the significance of species composition and community structure of grouped samples.

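### Patients and healthy controls enter under different drug washouts, so the baseline patient-versus-control microbiota comparison is open to confounding by recent antibiotic use

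*Protocol article*

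**What the plan says.** All statements are in the protocol article.

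- **CSU patients, Inclusion criteria, item 5.** Two washouts are set: "patients who have not taken any antihistamines within 2 weeks before entering the study, and have not used steroid hormones or immunosuppressants within the last"; the second of them lasts one month.
- **CSU patients, Exclusion criteria.** None of the seven items concerns a drug. The nearest one excludes "severe primary diseases, such as cardiovascular, liver, kidney, digestive, or hematopoietic conditions", which is about severe disease and not medication.
- **Healthy controls, Inclusion criteria, item 4.** The requirement is "no drug use for at least 15 days before entering the study", with no drug class singled out.
- **Study design.** Before treatment all 75 participants "will undergo clinical index evaluation, magnetic resonance scanning, and microflora collection".
- **Microbiota analysis.** Ordination methods will be used to "explore the differences in community structure between CSU patients and healthy people, and between the acupuncture group and sham acupuncture group". A t-test together with "MetaStat, and LEfSe, will be employed to test the significance of species composition and community structure of grouped samples" follows.
- **Table 1.** A medication record is ticked at every time point. The article does not say that it is used in eligibility or in the microbiota analysis.

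**The concern.** Antibiotics and antifungals act directly on the flora that the study measures. The patient washout covers urticaria drugs; the control washout covers every drug. The two rules differ between exactly the groups that the baseline microbiota analysis sets against each other. That comparison is not randomised, so nothing else in the design balances recent antimicrobial use between them.

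At stake is the interpretation of one mechanistic result. The Discussion presents the gut and skin microbiota as a way to describe the pathology of CSU. If some patients come with recent antimicrobial exposure and controls by rule do not, a shift in diversity or composition may be read as a feature of the disease when part of it comes from medication.

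**Working it through.** **Step 1: compare the written rules.**

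| Recent use before study entry | CSU patient | Healthy control |
|---|---|---|
| Antihistamine | barred, 2 weeks | barred, 15 days (any drug) |
| Steroid or immunosuppressant | barred, 1 month | barred, 15 days (any drug) |
| Antibiotic or antifungal | no restriction stated | barred, 15 days (any drug) |
| Probiotic as food or supplement | no restriction stated | unclear whether it counts as a drug |

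The third row is the firm asymmetry. The fourth is uncontrolled, but not clearly unequal.

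**Step 2: which analyses it reaches.** The baseline comparison of patients with healthy people crosses the two rules, so it is exposed. The acupuncture and sham arms are both patients under the same rule and are randomised. The Correlation analysis section is confined to patients and compares correlations between the two arms, so controls do not enter it.

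**Step 3: illustrative size.** The article states no exposure rate, effect size or power for the microbiota contrast, so there is no figure of its own to reproduce. Inputs:

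- Group sizes 50 and 25 (Sample size section).
- Two-sided 5% level, critical value 1.96. The level is stated for the clinical data and the correlations, and is assumed here.
- f, the share of patients recently exposed: assumed 5%, 10% or 20%; controls 0.
- D, the shift that exposure causes in a diversity index, in SD of unexposed people: assumed 0.5, 1.0 or 1.5.
- No true disease effect.

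Formulas:

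- bias = f × D
- SE = √[(1 + f(1 − f)D²)/50 + 1/25]
- false-positive rate = Φ(bias/SE − 1.96) + Φ(−bias/SE − 1.96)

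Worked case, f = 0.10 and D = 1.0: bias = 0.10; SE = √(1.09/50 + 0.04) = √0.0618 = 0.249; bias/SE = 0.402; rate = Φ(−1.558) + Φ(−2.362) = 0.060 + 0.009 = 6.9%.

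| Patients exposed | D = 0.5 | D = 1.0 | D = 1.5 |
|---|---|---|---|
| 5% | 5.1% | 5.5% | 6.0% |
| 10% | 5.5% | 6.9% | 9.1% |
| 20% | 6.9% | 12.5% | 21.2% |

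With f = 0 in both groups, which is what an equal rule aims at, the rate returns to 5.0%. The effect is slight if exposure is rare. It becomes material at around 20% exposure to something that moves the index by about 1 SD.

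**The case against.** The strongest reply has four parts.

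- **Nothing shows that any patient took antibiotics.** This stands. Both f and D are assumptions, and the mild cells of the table are close to 5%. A reader might infer that the contrast is confounded; the documents support only that it is open to confounding.
- **The timing is looser than it looks.** A reader might infer that patients may use antibiotics up to the day of sampling while controls are clean on that day. The documents do not support this. Both washouts count back from study entry. Table 1 ticks eligibility at Week -1 and sampling at Week 0. If entry means enrolment, neither rule covers drug use between the two. The asymmetry concerns use before entry.
- **The consequences can be overstated.** It is tempting to say that the bias carries into the network linking brain, microbiota and clinical indicators, or into the trial arms. It does not: that network contains patients only, and randomisation leaves the arms with chance imbalance and noise. A claim that probiotics are barred in controls but allowed in patients is also unsupported, since a probiotic may not count as a drug.
- **This is secondary, and a sensitivity analysis belongs in the analysis plan.** The primary outcome is UAS7, the microbiota comparison is described as exploratory, and medication is recorded. All true, and the absence of a stated sensitivity analysis is not itself the fault. But the point rests on two eligibility rules that are both written out and differ. An analysis plan can adjust afterwards; it cannot align the criteria.

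**Conclusion.** The point holds in a limited form. As written, the criteria admit a patient with recent antibiotic use and reject a control with the same history, which leaves the baseline gut and skin microbiota comparison between them open to confounding by antimicrobial use. The size cannot be determined from the article. Over the assumed range, a nominal 5% false-positive rate per index runs from 5.1% to about 21%, under a normal approximation with no exposed controls and no disease effect.

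The conclusion about the rules rests on the text alone; the size rests wholly on the assumed exposure and shift. It does not touch the primary outcome. It is a cheap improvement, not a flaw that undermines the trial.

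**What to change.** 1. Put one identical line in both sets of criteria: no systemic or topical antibiotic or antifungal for a fixed interval, counted back from the Week 0 stool and skin samples and not from entry. The 15 days already required of controls is the natural choice; the length is for the investigators to set.
2. State how probiotics are treated, in the same words for both groups.
3. Use the medication record in Table 1 to flag participants exposed before the Week 0 samples, or between Week 0 and Week 4, and repeat the microbiota comparisons without them.
4. If enrolment can no longer be changed, do step 3 alone and report how many participants were exposed in each group.

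This aligns only the agents that act directly on the flora. Other drugs stay unrestricted in patients and barred in controls before entry, so their use should be tabulated by group when the comparison is reported.

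The cost is one eligibility amendment and one extra analysis from data already collected. The downside is that a few patients are deferred or screened out. No one has treatment withheld, because the rule governs who is sampled and when.

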##### Pittsburgh sleep quality index

The PSQI comprises nine questions used to evaluate the effect of CSU on sleep quality. The evaluation includes sleep quality, sleep latency, sleep duration, sleep efficiency, sleep disorders, sleeping pills, and daytime dysfunction (32).

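### Drug criteria differ between patients and healthy controls, leaving the baseline patient-control imaging contrast open to confounding by centrally acting drugs

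*Protocol article*

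**What the plan says.** Under CSU patients, Inclusion criteria, item 5, patients must "have not taken any antihistamines within 2 weeks before entering the study, and have not used steroid hormones or immunosuppressants within the last month". No other drug class is named. The patient Exclusion criteria name no drug; the nearest item excludes people "diagnosed with a psychiatric illness".

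Under Healthy controls, Inclusion criteria, item 4, the rule covers every drug: "no drug use for at least 15 days before entering the study".

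Table 1 lists a "Medication record" at all four time points. The fMRI data analysis sections name no drug term; preprocessing mentions covariate regression without saying which covariates. The Region of interest section selects five seeds for their links to urticaria, disturbed sleep and mood disorder.

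The Introduction sets two aims. The first concerns treatment: "The primary objective of this study is thus to systematically elucidate the brain network mechanism associated with the treatment of CSU by acupuncture". The second is to understand the pathology of CSU, and the Discussion returns to it. Under Study design, controls are assessed only before treatment and only patients are reassessed afterwards.

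**The concern.** Drugs taken for sleep, mood or itch can act on the brain, and the main imaging measurement is resting connectivity from seeds tied to sleep and mood. If some patients are scanned while taking such a drug and every control is drug-free, drug use is associated with group by design. A difference in default mode network connectivity between patients and controls could then be partly a drug difference, reported as a feature of the disease. Controls are scanned once, so no later scan can separate the two explanations.

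**Working it through.** **Stated figure.** The article sets 50 patients and 25 controls from imaging precedent and says that the usual calculation does not apply. It gives no effect size, SD or power, so there is no figure to reproduce. The calculation below is for scale only.

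**Which contrast is affected**

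| Contrast | Aim served | Drug rules on entry | Expected baseline difference in drug use |
|---|---|---|---|
| Patients v controls, before treatment | CSU pathology | Different | Share of users in patients, minus 0 |
| Verum v sham, patients | Acupuncture mechanism | Same | 0 |

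I take the randomised comparison to be among patients, as in Randomization and blinding.

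**Inputs**
- From the Sample size section: 50 patients, 25 controls. With 1:1 allocation, 25 patients per arm.
- Two-sided 5% level: stated for the clinical data and correlations. The imaging threshold is not specified, so 5% is illustrative.
- Assumed, not in the documents: share of patients using a centrally acting drug, p = 10-20%; shift in a connectivity measure among users, d = 0.5-1.0 SD, in the same direction for all users.

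**Patient-control contrast**
- Bias = p × d. Low end 0.10 × 0.5 = 0.05 SD; high end 0.20 × 1.0 = 0.20 SD.
- SE = √(1/50 + 1/25) = √0.06 = 0.245 SD.
- False-positive rate = 1 − Φ(1.96 − bias/SE) + Φ(−1.96 − bias/SE).
- Bias 0.05: bias/SE = 0.204, rate 5.5%.
- Bias 0.20: bias/SE = 0.816, rate 12.9%.

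A wider grid, p = 10-40% and d = 0.3-0.8 SD, with the extra variance among patients included, gives biases of 0.03-0.32 SD and rates of 5.2-24.7%. At p = 20% and d = 0.5 the bias is 0.10 SD and the rate 6.9%.

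**Verum-sham contrast**
- Expected baseline bias: 0, whatever p and d are.
- SD of the chance imbalance in use = √(2p(1 − p)/25): √(0.18/25) = 8.5 percentage points at p = 10%, √(0.32/25) = 11.3 at p = 20%. This is ordinary random error.
- If use changes in 10-20 percentage points more patients in one arm during the 4 weeks, the shift at d = 0.5-1.0 is 0.10 × 0.5 = 0.05 SD to 0.20 × 1.0 = 0.20 SD. The difference between the patient and control criteria does not cause this.

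**Precision lost by leaving out flagged patients at baseline**
- 10% flagged: √(1/45 + 1/25) = 0.249 SD.
- 20% flagged: √(1/40 + 1/25) = 0.255 SD.
- Against 0.245 SD with all 50, the loss is small.

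**The case against.** The strongest reply is that the difference in criteria cannot touch the main question. That is right. A reader might infer that drug effects enter the contrast carrying the primary objective, but that objective concerns acupuncture treatment and rests on patients randomised under one set of drug rules. The Abstract does frame the mechanism as improving network dysfunction, and the baseline controls are the only healthy reference for dysfunction. This makes the baseline contrast relevant to interpretation, but it does not bias verum versus sham.

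A reader might also infer from the sleep index, whose listed areas include "sleep disorders, sleeping pills, and daytime dysfunction", that the investigators expect hypnotic use. They are only listing what the questionnaire covers. The listing shows that use would be measured, not that it is expected.

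The exclusions for psychiatric illness and severe primary disease narrow the group of likely users. Both p and d are assumptions, different drugs may shift a connection in different directions, and at the low end 5.5% against 5% is negligible. All of this stands.

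Finally, the full protocol or analysis plan may name drug covariates or hold further medication rules. The absence of a covariate from an article is no defect in itself. The point rests on what is printed: two numbered lists of criteria that treat the same drugs differently.

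**Conclusion.** The point holds for the baseline patient-control imaging contrast and no further. The criteria as printed allow centrally acting drugs in patients and bar them in controls, in an analysis seeded in regions chosen partly for their links to sleep and mood. Under the assumed 10-20% use and 0.5-1.0 SD effect, the bias is 0.05-0.20 SD and the false-positive rate per test about 5.5-13%; the true size is unknown. The contrast is non-randomised and serves the pathology aim, so this is a modest point, worth acting on because the remedy is cheap and the record it needs is already planned.

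**What to change.** 1. Reconcile item 5 of the patient inclusion criteria with item 4 of the control inclusion criteria as they bear on centrally acting drugs. Which classes and what window are for the sponsor to decide. The change concerns who is enrolled; nobody is asked to stop a drug.
2. Use the medication record to flag centrally acting drug use at the baseline scan, and repeat the patient-control contrasts without flagged patients or with use as a covariate. This also works for patients already enrolled.
3. For verum versus sham, keep all randomised patients and adjust at most for baseline use. Report changes in use during treatment by arm. Do not drop scans because of use after randomisation: use may change in response to treatment (for example, if sleep improves), and selecting on it could bias the randomised comparison.

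With full alignment, p = 0 and the drug-induced bias in the patient-control contrast disappears. The cost is one reconciled eligibility item, slightly slower recruitment and one extra sensitivity analysis on data already planned.
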